### Efficacy end-points

The composite primary outcome and the secondary outcomes will be collected for each patient. Diagnosis of complications will be made by the treating physicians. A data adjudication committee will review the appropriateness of the collected data for each outcome measure. Members of the committee will be blinded to the group allocation and comprise non-participating clinicians from each centre.

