## Methods

### Study design

Continuing vs withholding ACEIs/ARBs is a multi-centric, open-label, randomised controlled two-arm trial, with a 1:1 allocation of hypertensive patients undergoing major non-cardiac surgery to either continue or stop their ACEIs/ARBs. When admitted to the hospital, patients will be randomised to either continue their ACEIs/ARBs including on the day of surgery (group A) or discontinue the drugs 24–36 h before surgery (group B). The primary endpoint will be a composite outcome of all-cause 30-day mortality, major adverse cardiovascular events (acute myocardial infarction, stroke, arrhythmias requiring intervention, hypertensive crises, acute pulmonary oedema, postoperative cardiogenic shock), acute kidney injury, postoperative respiratory failure, sepsis and unplanned ICU admissions. The Standard Protocol Items: Recommendations for Interventional Trials (SPIRIT) checklist is provided in Additional file 2, and the schedule of the participant enrolment in the study (SPIRIT figure) is shown in Fig. 1.

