### Randomisation and blinding

All study patients will receive the same standards of care and management, including treatment of any harm resulting from the trial. However, they will receive no compensation as a result of participation in the study. They will be randomised to either continue with their ACEI/ARB treatment (including on the day of surgery) (group A) or to withhold it 24–36 h before surgery (group B) (two doses of the ACEI or ARB will be omitted to account for variation in the timing of administration, i.e. morning or evening). The patient’s blood pressure will be monitored periodically and treated with calcium channel blockers if necessary. Other antihypertensives that the patient may be concurrently receiving will be continued on the day of surgery. All such orders will also be recorded. Following surgery, anti-hypertensive medications including ACEIs/ARBs will be restarted at the earliest and the date of restarting anti-hypertensive therapy will be noted.

Randomisation will be carried out using permuted block randomisation (blocks of 20). The randomisation codes and sequence will be computer-generated by a statistician at each institute. The randomisation codes and the sequence will be kept secure at each participating centre. One code from a block sequence will be allotted each time when the patient is enrolled into the study. Allocation concealment will be with opaque sealed envelopes which will be opened 2 days before surgery. The diagnosis of outcomes will be made by clinicians treating the patients. The data for primary and secondary outcomes will be collected from the anaesthesia and surgical case records by the investigators and the project staff. The project staff will be trained by the investigators in the aspects of data collection and approach to missing data.

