### Clinical data

Baseline data such as age, gender, height, weight, BMI, ASA physical status, surgery, co-morbidities and anti-hypertensive medications will be collected. In-hospital mortality/mortality within 30 days of surgery, postoperative major adverse cardiovascular events (acute myocardial infarction, stroke, acute pulmonary oedema, postoperative cardiogenic shock, acute severe hypertension crisis, severe cardiac arrhythmia requiring therapeutic intervention), the incidence of intra- and postoperative (24 h) hypotension (systolic blood pressure < 90 mmHg), acute kidney injury (based on the serum creatinine item of the KDIGO criteria [9]; baseline serum creatinine will be the preoperative value), hyperkalaemia (serum potassium level > 5.5 meq/L requiring intervention), angioneurotic oedema, sepsis (suspected or culture-positive), postoperative respiratory failure and unplanned ICU admissions will be recorded.

The impact of withholding of ACEIs/ARBs on rebound pre-induction hypertension (blood pressure > 160/90 mmHg) on the day of surgery and case cancellation will also be evaluated. Intraoperatively, the episodes of hypotension will be treated with vasopressors (ephedrine, phenylephrine, norepinephrine and epinephrine). The choice of vasopressor will be left at the discretion of the anaesthesiologist. The lowest arterial pressure, duration of hypotension and total doses of vasopressors (bolus and infusion) will also be collected and reported. Other secondary outcomes noted will be myocardial injury (elevation of serum troponin-t evaluated till 12/24 h after surgery), duration of primary hospital stay and duration of ICU stay. The ancillary and post-trial care of the participants will be as per the standard of care for all patients admitted to the hospital for routine non-cardiac surgery, till their duration of stay in the hospital.

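### Clinicians who know the allocation diagnose the primary-endpoint events, and the blinded committee is described only as reviewing data already collected, which leaves the judgement-based components open to arm-dependent labelling

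*Protocol article*

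**What the plan says.** Study design describes a "multi-centric, open-label, randomised controlled two-arm trial, with a 1:1 allocation". Randomisation and blinding states "The diagnosis of outcomes will be made by clinicians treating the patients", and Efficacy end-points repeats it: "Diagnosis of complications will be made by the treating physicians". Outcome data are then "collected from the anaesthesia and surgical case records by the investigators and the project staff" (Randomisation and blinding); no blinding is stated for this step.

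The safeguard is in Efficacy end-points: "A data adjudication committee will review the appropriateness of the collected data for each outcome measure". On its make-up: "Members of the committee will be blinded to the group allocation and comprise non-participating clinicians from each centre".

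The composite (Objectives; Study design) joins death with acute myocardial infarction, stroke, arrhythmias that need intervention, hypertensive crises, pulmonary oedema, cardiogenic shock, acute kidney injury, respiratory failure, sepsis and unplanned ICU admission. Clinical data ties acute kidney injury to the serum creatinine item of KDIGO, with the preoperative value as baseline. It counts "sepsis (suspected or culture-positive") and gives no criteria for hypertensive crisis, pulmonary oedema or respiratory failure.

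On antihypertensive treatment around surgery, Randomisation and blinding adds "All such orders will also be recorded". It also has the date of restarting therapy noted.

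**The concern.** The order of events is stated: diagnosis by someone who knows the arm, extraction from the record, then blinded review. Blinding the last step does not by itself correct a difference between arms that arose at the first. A clinician who knows that a patient's drug was withheld, or continued, may suspect, test for, name or refer a complication more or less readily. An event that was never named may not appear among the outcome data that the committee is given.

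The exposure differs by component. Death hardly depends on labelling, and acute kidney injury follows a numerical rule wherever creatinine was measured. Hypertensive crisis, pulmonary oedema and respiratory failure have no criteria in the article. Arrhythmia requiring intervention and unplanned ICU admission are defined by the treating team's own decision. Suspected sepsis meets the protocol's definition as it stands, so a committee applying that definition has no stated ground to reject a case that rests on suspicion alone.

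The primary comparison is at stake. Differential labelling could produce a difference where there is none, or hide a real one.

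**Working it through.** **Inputs.** From Sample size calculation: 25% events in the reference group, a 21% relative reduction, 80% power, 2016 patients (2100 with dropouts), final nominal alpha 0.048. Sidedness is not stated; two-sided is assumed because one-sided versions do not reproduce the sample size. The labelling shortfall r is an assumption, since the documents give none.

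**The plan's own figure.** p1 = 0.25; p2 = 0.25 × 0.79 = 0.1975; difference 0.0525; mean 0.22375.

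n per arm = [1.977 × √(2 × 0.22375 × 0.77625) + 0.842 × √(0.25 × 0.75 + 0.1975 × 0.8025)]² / 0.0525² = 1001 after rounding up, or 2002 in total. This is within 0.7% of 2016, and power with 1008 per arm is 80.3%. The sample size is not in dispute.

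**Effect of a labelling shortfall with no true effect.** The true rate is 25% in both arms, and one arm loses a fraction r of its events to non-labelling. Its observed rate is 0.25(1 − r), so the false difference is d = 0.25r. With n = 1050 per arm (2100/2), c = 1.977 × SE₀, SE₀ from the pooled rate and SE₁ from the two observed rates:

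P(reject) = 1 − Φ((c − d)/SE₁) + Φ((−c − d)/SE₁)

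| r (assumed) | Observed rates | d | P(reject) |
|---|---|---|---|
| 0 | 25% v 25% | 0 | 0.048 |
| 4% | 25% v 24% | 1 point | 0.080 |
| 8% | 25% v 23% | 2 points | 0.184 |
| 12% | 25% v 22% | 3 points | 0.361 |

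For r = 8%: c = 0.0369, SE₁ = 0.0186, (0.0369 − 0.02)/0.0186 ≈ 0.90, upper tail about 0.18; the other tail is negligible.

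With 1008 per arm the picture is the same: r = 5% gives 9.7% and r = 10% gives 25.6%. A 10% shortfall is 2.5 points, about half of the planned 5.25.

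**If only some components are exposed.** The table applies r to all events. If half of the events were judgement-based (also an assumption), the same rows would need 4/0.5 = 8%, 16% or 24% of those events to go unlabelled in one arm.

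**The other direction.** If the planned effect is real and the shortfall falls on the reference arm, power with 1008 per arm drops from 80.3% to 57.9% (r = 5%) or 32.1% (r = 10%).

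These figures use an unadjusted two-proportion comparison at the final analysis and leave out the interim look.

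**The case against.** The strongest reply is that the text does not confine the committee to reported events. Efficacy end-points says that outcomes are collected for every patient and that the data for each outcome measure are reviewed, which could include patients with no reported event. Acute kidney injury can be recovered wherever creatinine was measured, and a review of appropriateness can strike out unsupported labels. A wide sepsis definition applies to both arms and creates no difference by its width alone. Packet content, redaction and case assignment may be set out in a fuller protocol or committee charter. The six-monthly independent audits (Auditing trial conduct) and central data checks (Strategies to ensure adequate enrolment and protocol compliance) bear on under-recording. The investigators' hypothesis favours withholding, but the Background and Discussion describe divided practice and conflicting guidelines, so no shared leaning among treating clinicians can be presumed.

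Much of this stands. A reader might infer that missed events can never be recovered, that soft labels pass through unchecked, or that the committee's blinding fails because orders are recorded and members come from each centre. The documents support none of these. They do not say that events without a report go unreviewed, that the committee sees the orders, or that members judge their own hospital's cases.

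What the reply does not remove is the stated rule: diagnosis rests with clinicians who know the arm, and no text gives the committee the task of searching for events or the power to add them. Audits of case record forms do not correct differences in suspicion.

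**Conclusion.** The point holds in a limited form. The article assigns diagnosis of the primary-endpoint components to unblinded clinicians and describes the blinded committee only as a reviewer of collected data. This is a stated design choice, not a detail left to an analysis plan. The judgement-based components are open to arm-dependent labelling; death and creatinine-defined acute kidney injury are much less so.

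The size and direction of any bias are unknown. The false-positive rates of about 8%, 18% and 36%, against 4.8%, follow arithmetically from assumed shortfalls of 4%, 8% and 12% of all events in one arm. They show how sensitive the comparison is, not what will happen. The change is worth making because small shortfalls matter at this sample size and, according to Trial status, recruitment has not begun.

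**What to change.** Amend Randomisation and blinding and Efficacy end-points as follows.

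1. Derive each component that has measurable criteria from the recorded values in every patient, whether or not a clinician made the diagnosis; for example, KDIGO acute kidney injury from all recorded creatinine values.
2. Send all triggered and all clinician-reported events to the existing blinded committee, and give it the final classification against fixed definitions, including one for suspected sepsis.
3. As a precaution, mask antihypertensive orders and restart dates in the packets, and assign each centre's cases to members from the other two centres.
4. Add a sensitivity analysis of the primary comparison restricted to the objective components, such as death and creatinine-defined acute kidney injury.

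The cost is a protocol and committee-procedure amendment, a programmed trigger list on data already collected, and more cases for the committee to read. No treatment, visit or sample size changes. Values that were never measured, and ICU referrals decided with knowledge of the arm, cannot be corrected in this way. The protocol should state that as a limitation.

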### Strategies to ensure adequate enrolment and protocol compliance

Case record forms will be uploaded into a secure database at the trial coordination centre in a time-bound manner. This will allow regular checks for enrolment rates, data accuracy and protocol adherence. Each centre will need to recruit approximately 700 patients. The study duration will be for a period of 3 years, extendable by 1 year in case the sample size is not met. We will perform an interim analysis after 1000 patients to assess the futility or harm of the trial. The O’Brien/Fleming method for interim analysis will be used [10].

### Auditing trial conduct

Auditing of the trial at each site will be carried out at 6-monthly intervals. The trial auditors will be independent of the investigators and comprise representatives from the Institutional Review Board. Trial auditing will be done with respect to accuracy and completeness of case record forms, verification of informed consent process and documentation, adverse event reporting and protocol adherence.

### Data safety and monitoring board

DSMB meetings will be held twice or thrice a year as per the institutional policy, and any occurrence of adverse events during the study will be discussed and necessary action will be taken. In general, the following aspects will be addressed by the DSMB.Monitoring safe and effective conduct of treatments of the study participantsAnalysis of adverse eventsIf necessary, recommending early conclusion of a trial when significant benefits or risks have been demonstratedBlinded trial interim result analysis

### Statistical analysis

To adjust for confounders, a multivariate logistic regression analysis will be carried out, stratifying for ASA physical status, age, gender, general vs neuraxial anaesthesia and types of surgery. Data will be also stratified according to the centre. Attempts to account for missing data will be made, but since this will be an intention to treat analysis, all data that will be available from each patient will be included in the study.

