## Background

Annually, more than 280 million people undergo non-cardiac surgery [1]. The mortality rate following non-cardiac surgery is 0.3% [2]. This risk is higher in patients with ischaemic heart disease, diabetes and hypertension. The perioperative period is the most vulnerable period to develop cardiac or vascular complications which are seen in 25% of patients undergoing major abdominal, vascular and orthopaedic surgeries [2]. More than 1/3 of the patients coming for non-cardiac surgery who present with hypertension may be receiving angiotensin-converting enzyme inhibitors (ACEIs)/angiotensin II receptor blockers (ARBs) which are commonly prescribed as first-line anti-hypertensive medications, the advantage being that these drugs modulate the renin-angiotensin-aldosterone axis and are considered cardioprotective [3]. In addition, ACEIs/ARBs are also used to treat patients with chronic left ventricular dysfunction and those with diabetic nephropathy. However, blunting of the renin-angiotensin-aldosterone axis may cause hypotension during induction of anaesthesia [3].

Continuation of ACEIs/ARBS in the perioperative period is associated with intraoperative and postoperative hypotension, and thus, many clinicians choose to withhold administration of these drugs [4]. However, this is often based on individual practice and has no relation to the profile of the patient and/or the surgery performed [3]. In addition, there is variation in practice with regard to the time of discontinuation with some clinicians discontinuing the drugs 24 h before surgery while some others choose to skip a morning dose of the drug. This in turn is not related to the pharmacokinetic or pharmacodynamic properties of the drugs. Other evidence points to the beneficial effects of a continuation of these drugs in the perioperative period with the demonstration of improved outcomes [5]. While perioperative hypotension is certainly a concern with the continuation of ACEIs/ARBs, discontinuation of these drugs before surgery makes patients susceptible to postoperative hypertension when the effects of anaesthetics wear off, and this may cause harm by increasing the risk of myocardial ischaemia [6]. In fact, postoperative hypertension is more frequently seen in those with preoperative hypertension and is known to increase the risk of occurrence of major adverse cardiovascular events [7].

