### Sample size calculation

Based on an incidence of 25% of the primary endpoint in the reference group [11], a total of 2016 patients will allow an 80% power to detect a 21% relative decrease of complications in the experimental group. To account for dropouts, a total of 2100 patients (700 at each centre) will be included. The analysis will be an intention-to-treat analysis. Since one interim analysis will be planned after recruiting 1000 patients according to the O’Brien and Fleming method, the interim alpha will be set at 0.0052 and the final nominal alpha at 0.048 (Additional file 1). The *P* values and respective sample sizes were based on a final sample size of 2100, and 1 interim analysis at halfway point was calculated using the “gsDesign” package of the R statistical software v4.0.0 (R Statistical Corp, Vienna, Austria).

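### The regression adjusts for general versus neuraxial anaesthesia, but nothing says the technique is fixed or recorded before allocation is known

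*Protocol article*

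**What the plan says.** The Statistical analysis section of the protocol article states the purpose and the type of model: "To adjust for confounders, a multivariate logistic regression analysis will be carried out". The covariates that the section then names for this model are given as "stratifying for ASA physical status, age, gender, general vs neuraxial anaesthesia and types of surgery". Centre is added as a further stratification factor. No other between-group analysis is described, although this one is not labelled primary.

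Four other places bear on the anaesthesia term:

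- **Study design:** the trial is a "multi-centric, open-label, randomised controlled two-arm trial, with a 1:1 allocation".
- **Randomisation and blinding:** "Allocation concealment will be with opaque sealed envelopes which will be opened 2 days before surgery". Randomisation is in permuted blocks of 20 with a sequence generated at each institute. No stratification by technique is described.
- **Participants:** both general and neuraxial anaesthesia are eligible.
- **Clinical data:** the examples of baseline data include ASA status, age, gender and surgery, but not anaesthetic technique.

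The Sample size calculation section states: "The analysis will be an intention-to-treat analysis".

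**The concern.** ASA status, age, gender, type of surgery and centre are settled before the envelope is opened. Anaesthetic technique need not be. Anaesthesia is given after allocation is known, in a trial where staff are not blinded. The Background gives a possible reason for allocation to influence the choice, since it says that "blunting of the renin-angiotensin-aldosterone axis may cause hypotension during induction of anaesthesia".

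A variable that follows randomisation is not a confounder of the randomised comparison. If allocation influences technique, adjusting for the technique given can do harm in two ways:

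1. Any part of the treatment effect that acts through technique is removed from the estimate.
2. If unmeasured severity drives both technique and outcome, patients who had the same technique in the two arms are no longer comparable, and a bias appears that the unadjusted comparison does not have.

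There is also a practical problem. Case cancellation is a studied outcome, and the Study hypothesis section links it to rebound hypertension after withholding. A patient randomised and then cancelled has no technique given, so a model that needs this covariate must drop or impute that patient, possibly more often in one arm.

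**Working it through.** **1. The plan's own figure.** The stated basis is 25% in the reference group, "80% power to detect a 21% relative decrease of complications in the experimental group", a final nominal alpha of 0.048 and 2016 patients.

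- Experimental rate: 0.25 × 0.79 = 0.1975; difference 0.0525; mean rate 0.22375.
- n per arm = [z(α/2)·√(2·p̄·q̄) + z(β)·√(p1q1 + p2q2)]² / difference², taking alpha as two-sided (the text does not say).
- = [1.977 × 0.5894 + 0.8416 × 0.5882]² / 0.0525² = 1001, so 2002 in total against 2016 stated. Power at 1008 per arm is 80.3%.

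The figure reproduces and this point does not alter it. It is the size for a comparison of two proportions, so it does not show whether an adjusted or an unadjusted analysis is primary.

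**2. Order of events.** Enrolment takes place at the preoperative visit, the envelope is opened 2 days before surgery, and anaesthesia is given at surgery. Technique as planned could be recorded before the envelope is opened. Technique as given comes after it. The covariate list does not say which is meant.

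**3. Illustration of size (assumptions, not trial data).** The documents give no rate of general anaesthesia by arm. Assume 1:1 allocation, no direct treatment effect, an unmeasured binary severity factor U (prevalence 50%), and logit P(event) = −1.9 + 1.2U. The event rate is then (0.130 + 0.332)/2 = 23.1% in each arm.

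*(a) Allocation does not shift technique.* Adjusted OR = 1.00; no bias.

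*(b) Allocation and U shift technique; technique has no effect on outcome.* Take logit P(general) = 1.5 − 1.5U in one arm and 0.7 − 1.5U in the other.

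- General anaesthesia: (0.818 + 0.500)/2 = 65.9% versus (0.668 + 0.310)/2 = 48.9%.
- Share with U = 1 among general-anaesthesia patients: 0.500/1.318 = 37.9% versus 0.310/0.978 = 31.7%. Event rates 20.7% versus 19.4%; OR 0.924.
- Share with U = 1 among neuraxial patients: 73.3% versus 67.5%. Event rates 27.8% versus 26.6%; OR 0.943.
- Adjusted OR 0.933, although the true OR is 1.00.

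The SE of the log OR at 1008 per arm and 23.1% in both arms is √[2/(1008 × 0.231 × 0.769)] = 0.106.

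| General anaesthesia by arm | True OR | Adjusted OR | abs(ln OR)/SE |
|---|---|---|---|
| 66% vs 58% | 1.00 | 0.967 | 0.034/0.106 = 0.3 |
| 66% vs 49% | 1.00 | 0.933 | 0.069/0.106 = 0.7 |
| 66% vs 34% | 1.00 | 0.880 | 0.128/0.106 = 1.2 |

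Swapping the arms inverts these (1/0.933 = 1.07), so the direction depends on which arm receives more general anaesthesia and which technique sicker patients receive. A separate simulation with continuous severity (log-odds 0.8 per SD on both outcome and technique) moved the OR from 1.00 to about 1.045 for a 9-point difference and 1.10 for 17 points.

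*(c) Allocation shifts technique, technique affects outcome (log OR 0.5), and U does not drive technique.* With general anaesthesia 69% versus 60%, 50% or 33%, total effects of OR 0.96, 0.92 or 0.85 are each adjusted away to 1.00.

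**The case against.** Much of the case on the other side stands.

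- **The protocol does not say that the technique given is used.** The Participants section uses technique to describe who is enrolled, so the planned technique may be meant. The baseline list is introduced as examples and is not exhaustive. This stands: the fault is that the covariate is left open to a harmful reading, not that the harmful version is stated.
- **The model is not called main or primary.** A reader might infer that the trial's headline result will carry this bias. The text does not support that: the analysis plan is not shown, and the sample size fits an unadjusted test equally well.
- **The route from allocation to technique is inferred.** The Background mentions hypotension at induction, not a change of technique. The Clinical data section has intraoperative hypotension treated with vasopressors. The Discussion reports similar hypotension in both groups of the observational study it cites. Where type of surgery dictates technique, any shift would be small. This limits the point to a possibility.
- **The size is assumed.** The illustration has no other covariates. ASA status, age and type of surgery would absorb some of the severity, and the smaller shifts give a bias well under one standard error.

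A reader might also infer that a logistic model is wrong for a trial sized on a relative risk decrease. That does not follow. Logistic regression for a trial sized on proportions is routine, and the Statistical analysis section names no effect measure.

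What the objections do not remove is that the covariate is named in the only model described, for a purpose that a post-allocation variable cannot serve, and that nothing in the article ties it to a time before allocation is known.

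**Conclusion.** The point holds as a conditional one. As worded, the covariate can be taken as the technique actually given. That would be a post-randomisation variable in an open-label trial, and adjusting for it could remove part of the effect or introduce bias. The bias is zero if allocation does not shift technique. The documents give neither its size nor its direction; the odds ratios above rest entirely on the assumed severity model and the assumed arm differences, and show only that moderate shifts would matter modestly.

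The difficulty with cancelled patients does not depend on any shift in technique: anyone randomised and never anaesthetised lacks the value. The documents give no expected number of cancellations, so this too is unsized.

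No claim is made that the trial's result will be biased. The plan should be corrected because the ambiguity is avoidable and the remedy is nearly free.

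**What to change.** In the Statistical analysis section, replace the anaesthesia term with the technique planned at the preoperative visit and recorded before the envelope is opened, or drop it. Keep ASA status, age, gender, type of surgery and centre. Report the technique actually given by arm, descriptively or in a sensitivity analysis only.

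The cost is one case report form field and one sentence of text. Adjustment will be slightly less precise where the plan later changes. The sample size, alpha and patient care are unaffected. The Trial status section says recruitment has not begun, and the Protocol amendments section already gives a route for a change to the analyses once the trial has started.

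### The covariate list for the only regression the protocol names omits ischaemic heart disease, diabetes and preoperative creatinine, so a modest, almost free gain in power is forgone

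*Protocol article*

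**What the plan says.** The Statistical analysis section gives one model, a logistic regression intended to deal with confounders, "stratifying for ASA physical status, age, gender, general vs neuraxial anaesthesia and types of surgery". It adds that the data are also stratified by centre. It does not call this model the primary analysis, but names no other method for comparing the groups.

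Three other places bear on the list:

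- The Background gives the mortality rate after non-cardiac surgery and continues: "This risk is higher in patients with ischaemic heart disease, diabetes and hypertension". The trial enrols hypertensive patients, so heart disease and diabetes are the two of these factors that can vary usefully within it.
- The Clinical data section states: "Baseline data such as age, gender, height, weight, BMI, ASA physical status, surgery, co-morbidities and anti-hypertensive medications will be collected". Heart disease and diabetes are not itemised there but fall under co-morbidities. The same section makes the preoperative creatinine the baseline for diagnosing acute kidney injury, which the Study design section includes in the primary composite.
- The Sample size calculation section claims "80% power to detect a 21% relative decrease of complications in the experimental group" and takes no credit for covariate adjustment.

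**The concern.** Adjusting for baseline variables that predict the outcome usually raises the power of a randomised comparison and protects against chance imbalance in them. The protocol names two risk factors, and collects a third variable that enters the definition of an outcome component, yet none of the three is in the model. The exclusion criteria remove only an eGFR below 15 mL/min/1.73 m² or renal replacement therapy, so patients can enter with anything from normal to severely reduced renal function.

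The verb is also loose. A regression that is *stratifying for* age and four other factors could mean main-effect adjustment, a conditional analysis within strata, or subgroup analyses.

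At stake is some power on the primary endpoint and the clarity of the model, not the validity of the comparison.

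**Working it through.** **1. Does the plan reach its power without covariates?**

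Inputs from the protocol article:
- "Based on an incidence of 25% of the primary endpoint in the reference group", so p1 = 0.25.
- A 21% relative decrease, so p2 = 0.25 × 0.79 = 0.1975 and the difference is 0.0525.
- Design: "with a 1:1 allocation of hypertensive patients".
- Alpha: "the interim alpha will be set at 0.0052 and the final nominal alpha at 0.048". Sidedness is not stated; two-sided is assumed. At half information this pair gives 0.0500 overall.

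Formula, per arm, with p̄ = 0.22375:

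n = [z(1−α/2)·√(2p̄(1−p̄)) + z(0.80)·√(p1(1−p1) + p2(1−p2))]² / (p1−p2)²

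At α = 0.048: [1.977 × 0.5894 + 0.842 × 0.5882]² / 0.0525² gives 1001 per arm, 2002 in total. The plan states "a total of 2016 patients will allow an 80% power", which is within 1%. At 1008 per arm the unadjusted power is 80.3%. Expected events are 1008 × (0.25 + 0.1975) ≈ 451.

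The stated power therefore does not depend on any covariate.

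**2. What would the three extra variables add?**

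The documents give no prevalence or odds ratio for them, so every value here is an assumption. Logistic regression was simulated with 2016 patients, marginal rates of 25% and 19.75%, alpha 0.048 and 1500 runs per row. The listed covariates were represented by one prognostic score with SD 0.4 or 0.8 on the log-odds scale. Assumed prevalences were 15–20% for heart disease, 40% for diabetes and 15–20% for raised creatinine.

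| Assumed odds ratios (heart disease / diabetes / creatinine) | Score SD | Unadjusted | Listed | Listed + three | Change, points |
|---|---|---|---|---|---|
| Weak: 1.3 / 1.2 / 1.5 | 0.4 | 81.8% | 82.7% | 82.9% | +0.2 |
| Weak | 0.8 | 80.3% | 84.9% | 84.7% | −0.2 |
| Moderate: 1.6 / 1.4 / 2.0 | 0.4 | 80.8% | 81.5% | 82.0% | +0.5 |
| Moderate | 0.8 | 80.3% | 83.9% | 84.6% | +0.7 |
| Strong: 2.0 / 1.6 / 3.0 | 0.4 | 80.1% | 81.1% | 83.6% | +2.5 |
| Strong | 0.8 | 79.9% | 84.0% | 86.7% | +2.7 |

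Each power has a simulation standard error of about √(0.83 × 0.17 / 1500) ≈ 1 point. The models were fitted to the same data sets, so the differences are less noisy than that. The weak rows amount to no gain.

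A second simulation (3000 runs per set) modelled ASA, age, sex and surgery type separately, with assumed c-statistics of 0.66, 0.70 and 0.75. Adding the three variables raised power from 81.5% to 82.4%, from 82.3% to 84.0% and from 83.4% to 85.9%, that is by 0.9, 1.7 and 2.5 points. Anaesthesia type and centre had no effect there, so its reduced model may understate what the planned one recovers.

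**3. Cross-check.** With effective n = n/(1−R²), starting from 80.3%, an incremental R² of 0.01, 0.02, 0.05 and 0.10 gives 80.7%, 81.1%, 82.3% and 84.3%. In patients, R² = 0.02 is worth 2016/0.98 − 2016 ≈ 41 and R² = 0.05 is worth 2016/0.95 − 2016 ≈ 106. The dropout allowance is 2100 − 2016 = 84.

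**4. Where the gain comes from.** The marginal odds ratio is (0.1975/0.8025)/(0.25/0.75) = 0.738. The conditional odds ratios in the first simulation were 0.731 to 0.702. Power rises because the conditional odds ratio lies further from 1, not because the standard error of its logarithm shrinks.

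**The case against.** The strongest reply is that nothing here is an error. The plan's power is met unadjusted, randomisation protects the comparison, and the benefit rests on assumed effect sizes. ASA status already grades systemic disease and overlaps with heart disease and diabetes. The exclusions remove the extremes of renal function and patients treated for left ventricular dysfunction. All of that stands. It makes this an efficiency improvement and limits its size.

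Chance imbalance is also a weak argument at this sample size. For a factor with 20% prevalence, the SD of the difference between arms is √(2 × 0.2 × 0.8 / 1008) ≈ 1.8 points. With an assumed odds ratio of 2.0, that shifts the event rate by roughly 0.25 points, against a target difference of 5.25.

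A further reply is that an article may leave covariates to a fuller document. That would answer a complaint about silence. Here the article names specific variables, so the selection itself can be improved, although whether the list is closed is an inference.

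A reader might infer more than the documents support:

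- *The primary analysis is misspecified.* The text never calls this regression primary.
- *The protocol ignores three risk factors it names.* It names two, and with respect to mortality, not the composite. Creatinine appears only as the reference for acute kidney injury.
- *Precision is lost.* For a conditional log odds ratio the right word is power. A gain in precision would apply to a standardised risk difference or risk ratio.
- *The analysis splits into hundreds of sparse cells.* The sentence speaks of adjusting for confounders by regression, so model adjustment is the natural reading. The documents give neither age bands nor level counts.

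**Conclusion.** The point holds as a low-cost improvement. The only regression named leaves out two risk factors that the protocol itself cites and a baseline value on which one outcome component is judged, although the data are to be collected. There is no bias, no type I error problem and no shortfall against the stated 80% power.

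The forgone gain is about 0 to 3 percentage points of power, over and above what the listed covariates already bring. That range depends entirely on assumed prevalences and odds ratios and on how much ASA status already captures. Under weak effects it is nil, and the documents do not allow it to be narrowed.

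**What to change.** In the Statistical analysis section, replace *stratifying for* by *adjusting for* and pre-specify one logistic model with treatment, centre and main-effect baseline covariates fixed before randomisation:

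- age as a continuous term, sex and ASA status;
- planned surgery type and planned, not actual, type of anaesthesia. Treatment is open-label and envelopes are opened 2 days before surgery, so the technique used could be settled once allocation is known;
- ischaemic heart disease and diabetes, each as its own item on the case report form;
- preoperative creatinine or eGFR.

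The cost is one rewritten sentence, itemising two co-morbidities, and a few more model terms, which is negligible with about 450 expected events. The Trial status section says recruitment has not begun, so the change can precede any outcome data. Once the trial has started, the Protocol amendments section requires ethics approval and a registry update for a change to the analyses.
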